#### Process evaluation

Descriptive analyses will be conducted to summarize response rates, overall experiences regarding the ESM intervention and the PsyMate, and additional findings with respect to the sampling and intervention quality.

### Confidentiality

All study-related information will be stored securely at the study site. All participant information will be identified by a coded ID number to maintain participant confidentiality. The principal investigators and project team members will be able to access the data. All records that contain names or other personal identifiers (e.g. informed consent forms) will be stored separately from study records identified by code number. All datasets will be password protected.

### Monitoring and participant safety

The study will be monitored externally by the trial monitoring committee of the MUMC+ (Clinical Trial Center Maastricht). The trial monitoring committee is independent of the study organizers. All adverse events (AEs) and serious adverse events (SAEs) that occur during the study will be recorded during the (feedback) sessions, the post-intervention assessment, and the two- and six-month follow-up assessment. SAEs will be reported to the accredited Medical Ethical Committee that approved the protocol.

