#### Intervention period

##### Experimental group

Caregivers in the experimental group will participate in the 6-week intervention ‘Partner in Sight’ and collect ESM data for three consecutive days a week. Every two weeks they will receive ESM-derived feedback in a face-to-face session with a coach in their home or at the MUMC+ according to their preference. This sums up to a total of three feedback sessions. The aim of the feedback sessions is to provide an overview of the caregiver’s everyday functioning, including their mood (i.e. levels of positive affect), daily life activities, and social interactions. The focus will be on positive rather than negative emotional experiences and how these relate to specific daily contexts. In this way, we try stimulate caregivers to redirect their behavior towards situations that elicit positive emotions.

At the beginning of each feedback session average levels of positive affect experienced during the past two weeks will be presented. Subsequently, a feedback module on *daily activities* and/or *social interactions in daily life* will be discussed with the caregiver. Feedback modules are based on an existing ESM intervention, which has proven to be effective in people with depression [9]. During the first feedback session the module ‘*daily activities’* will be discussed with the caregiver. The data may, for example, illustrate that positive emotions increase during moments of active relaxation, while the caregiver is actually spending the least amount of time on active relaxation activities. The coach will stimulate caregivers to think about the findings and to implement new insights into their daily lives. In the second feedback session the module ‘*social interactions in daily life’* will be added. A caregiver might state, for example, that he prefers to spend his time alone, without any company. The feedback, however, may show that positive emotions are experienced particularly while being in company instead of when being alone. This finding might induce an increase in social interactions, which in turn may lead to increased positive emotions. The third session will combine both modules. At the end of each session the weekly progress in levels of positive affect yielded by daily activities and/or social interactions will be evaluated. A more detailed description of the feedback modules is presented in Table 1.

**Table 1 Tab1:** Feedback modules of the intervention ‘Partner in Sight’

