##### Pseudo-experimental group

A pseudo-experimental group is added to the study design to investigate whether the ESM-derived feedback adds value to the use of the PsyMate without receiving any direct feedback. Repeated self-assessments might already increase caregivers’ self-awareness and redirect their behavior accordingly [21].

Caregivers in the pseudo-experimental group will participate in a 6-week pseudo-intervention and collect ESM data for three days a week. Every two weeks they will receive a face-to-face session with a coach. However, during these sessions they will not be provided with feedback on their daily recordings. Alternatively, a semi-structured interview on their well-being during the past two weeks will be performed to prevent any effects of different duration of contact with the coach.

At the end of each session caregivers will, similar to the participants in the experimental group, be provided with a debriefing concerning the use of the ESM-device.

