##### Control group

Caregivers in the control group will receive care as usual during the 6-week intervention period. Care conditions will differ among caregivers and will be registered carefully at baseline. In general, care as usual includes low-frequent sessions with a clinician from the memory clinic or counselor from a caregiver support service.

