#### Follow-up assessments (T2 & T3)

A two- and six-month follow-up assessment will be administered in which participants receive a number of retrospective questionnaires by post and are asked to return them after completion.

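### Adverse events are to be recorded at coach sessions that only the two ESM arms have, so the opportunity to record them before T1 is 4 vs 4 vs 1

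*Protocol article*

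**What the plan says.** The section Monitoring and participant safety sets a broad scope, "All adverse events (AEs) and serious adverse events (SAEs) that occur during the study will be recorded", and then names the occasions: events "will be recorded during the (feedback) sessions, the post-intervention assessment, and the two- and six-month follow-up assessment". The brackets around the word feedback indicate that the coach sessions of both ESM arms are meant.

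The arms differ in whether they have such sessions:

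- Experimental group: a session every two weeks over six weeks. The section states "This sums up to a total of three feedback sessions".
- Pseudo-experimental group: "Every two weeks they will receive a face-to-face session with a coach", also over six weeks, so three sessions.
- Control group: "Caregivers in the control group will receive care as usual during the 6-week intervention period". No study visit or call is described between baseline and T1.

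T1 is held in person in all arms, at home or at the centre. At T2 and T3, "participants receive a number of retrospective questionnaires by post and are asked to return them after completion", again in all arms.

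**The concern.** The recording rule is the same sentence for everyone, but it is tied partly to visits that belong to the intervention. Following it as written means that caregivers in the ESM arms can report an event about two weeks after it happened at the latest, while control caregivers may have to remember it for up to six weeks. The setting differs too: before T1, ESM-arm events come up in meetings with the coach who delivers the allocated condition, whereas control-arm events are collected only at T1, which the Randomization section gives to a blinded research assistant.

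What is at stake is the reading of any adverse-event table by arm. An apparent excess under ESM could come from closer questioning alone, and a real excess could be dismissed for the same reason. The comparison affected is ESM (either arm) against control.

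**Working it through.** **Step 1. Reproduce the plan's own figure.** Six weeks divided by one session per two weeks = 3 sessions, as the Experimental group section states. The same interval and duration give 3 in the pseudo-experimental arm.

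**Step 2. Count recording occasions after baseline.**

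| Occasion | Experimental | Pseudo-experimental | Control |
|---|---|---|---|
| Coach sessions | 3 | 3 | 0 |
| T1 | 1 | 1 | 1 |
| Up to T1 | 4 | 4 | 1 |
| T2 and T3 | 2 | 2 | 2 |
| Total | 6 | 6 | 3 |

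**Step 3. Illustrate the effect on counts.** The documents give no adverse-event rate and no recall figure, so the following rests on assumptions: equal true rates in all arms, events spread evenly over time, each event reported (if at all) at the next occasion, and reporting probability falling exponentially with half-life h. The mean proportion captured over a recall window of L weeks is

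f(L) = (1 − exp(−kL)) / (kL), with k = ln 2 / h.

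In the intervention period L is 2 weeks in the ESM arms and 6 weeks in control.

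| h (weeks) | f(2), ESM | f(6), control | Ratio |
|---|---|---|---|
| 2 | 0.721 | 0.421 | 1.71 |
| 4 | 0.845 | 0.622 | 1.36 |
| 8 | 0.918 | 0.780 | 1.18 |
| 16 | 0.958 | 0.881 | 1.09 |
| perfect recall | 1 | 1 | 1.00 |

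**Step 4. Extend to the whole study.** T2 and T3 fall two and six months after the intervention (Study aims), so the later recall windows are about 8.7 weeks (T1 to T2) and 17.4 weeks (T2 to T3), the same in all arms. The ratio is

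[6·f(2) + 8.7·f(8.7) + 17.4·f(17.4)] / [6·f(6) + 8.7·f(8.7) + 17.4·f(17.4)].

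It is 1.22, 1.10, 1.04 and 1.02 for h = 2, 4, 8 and 16 weeks, and 1.00 with perfect recall. The imbalance is diluted because the arms are treated alike after T1.

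**The case against.** The strongest reply is that the analysis sections plan no between-arm test of adverse events, and that the safety section is about monitoring and reporting of serious events under an external committee. The half-lives above are assumed and suit minor events; a serious event is likely to be remembered at T1. The Resource Utilization in Dementia questionnaire also asks about resource use in every arm at T1, T2 and T3, which may bring some admissions to light. All of this stands, and it is why the point is minor. It does not remove the imbalance, which follows from a stated rule and not from detail that a condensed article leaves out.

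A reader might infer more, and the documents do not support it:

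- *That most of the observation time is not covered, because follow-up is postal.* The safety section names both follow-up assessments as recording points and claims all events during the study. The Randomization section has a research assistant conduct the follow-up assessments.
- *That T2 and T3 carry no adverse-event instrument, because Table 2 lists none.* Table 2 lists no adverse-event form at any visit, including the sessions and T1, where recording is plainly intended. Its silence therefore shows nothing about T2 and T3.
- *That the pseudo-experimental arm would report more than the experimental arm*, because in the former "a semi-structured interview on their well-being during the past two weeks will be performed" and in the latter "The focus will be on positive rather than negative emotional experiences". These describe session content, not adverse-event enquiry. Session numbers are equal, and both arms end sessions with a similar debriefing.
- *That about 22 of 90 caregivers (0.25 × 90 = 22.5) would have no late safety information.* The 25% loss in the Sample size section is a planning allowance with no timing attached.

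**Conclusion.** The point holds as an imbalance of opportunity. As written, the rule gives each ESM arm three recording occasions before T1 that control lacks: 4 vs 4 vs 1 up to T1, and 6 vs 6 vs 3 overall. Counts would differ for this reason only if recall at T1 is incomplete. In that case the direction is towards more events in the ESM arms, by a factor of about 1.2 to 1.7 in the intervention period and about 1.04 to 1.2 over the study for half-lives of 8 down to 2 weeks. Those factors depend on the assumed recall model; the counts of occasions do not, beyond taking the article's silence on control-arm contact before T1 at face value. The comparison of experimental with pseudo-experimental is not affected by the number of occasions. Severity: minor.

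**What to change.** Ask the same short set of adverse-event and serious-adverse-event questions in all three arms at T1 (covering T0 to T1), T2 and T3, and include them in the postal packs. State that any between-arm summary of adverse events uses only these common time points. Keep recording events at coach sessions for safety, but list those first noted there separately as non-comparative.

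The cost is about one page in three existing assessments and one sentence in the reporting plan. The downside is a slightly longer assessment and postal pack. Design, sample size and intervention are unchanged.

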### Withdrawal of participants

Participants can leave the study at any time without justification, and without any consequences.

## Discussion

The current paper presents the study protocol of an RCT to evaluate the effectiveness of an ESM intervention to improve caregivers’ sense of competence and control, and psychological well-being. The potential effects of the intervention may help caregivers to keep on caring and prevent them from developing (more) health problems and becoming overburdened. This study contains several unique aspects. To our knowledge, this is the first ESM intervention for caregivers of PwD. ESM might be a promising tool in both research and clinical practice, since it offers the possibility to provide more detailed information on caregiver functioning in the flow of daily life. In this study we will use ESM as an intervention tool, but also as an assessment tool to evaluate the effects of the intervention. Therefore, an important advantage is that the results of this study represent a high level of ecological validity. Another unique aspect is that our intervention focuses on positive rather than negative experiences during the caretaking process. Positive emotions are important facilitators of adaptive coping and might increase caregivers’ feelings of being capable to care [18, 50]. The ESM intervention might enhance caregivers’ self-awareness and redirect their behavior to situations that are conducive to positive emotional experiences. Moreover, the intervention includes ESM-derived feedback that is tailored to the caregivers’ personal situation and actively involves them in their own empowering process. Both are known to be important aspects of effective caregiver support interventions [14]. The inclusion of a pseudo-experimental condition in our study design allows us to unravel the added value of the ESM-derived feedback to the use of the PsyMate in general. Caregivers might benefit from the use of the PsyMate without receiving any feedback, since repeated self-assessments may lead people to pay more attention to their internal states and own behavior [21]. Lastly, the intervention program will be delivered in daily practice and offers the possibility to be integrated in future clinical practice. The additional process and economic evaluation will provide valuable information on potential facilitators and barriers to implementation, and on the cost-effectiveness of the intervention.

Certain limitations need to be acknowledged in advance. There is a possibility of sample bias. Although participants will be recruited in a wide range of different institutions, the group that agrees to participate in the study might differ from the group that refuses to participate. In general, participants are expected to be relatively young, more highly educated, and more pro-active in seeking for support [51]. Moreover, recent results from our feasibility study, in which caregiver were asked to collect ESM data for only six consecutive days, showed that a large number of caregivers refused to participate because of a too busy time schedule ([name] et al.: Dealing with daily challenges in dementia (Deal-id study): an innovative approach to assess caregiver functioning in the flow of daily life, submitted). The even more time-intensive nature of the current study might, therefore, cause a selection bias towards caregivers that are not yet facing extreme difficulties in the caregiving process. It is also expected that a number of participants will drop out of the ESM intervention prematurely. In this specific population, it is likely that participants drop out for specific disease related reasons, such as institutionalization or death of the PwD. In a previous ESM study with persons with depression, 15 % of the participants did not complete the 6-week ESM intervention period [9]. The face-to-face sessions with a coach and the delivery of personalized feedback, however, might increase caregivers’ motivation to participate given that usual care for dementia caregivers often does not, or very infrequent, include counseling [52].

In conclusion, the results of this study will provide a valuable contribution to the growing knowledge on m-health interventions for caregivers of PwD. Our ESM intervention ‘Partner in Sight’ is expected to be effective in terms of caregiver well-being and might be an innovative approach to support caregivers of PwD in managing daily challenges during the course of the disease.

### Ethics approval and consent to participate

The Medical Ethical Committee of the MUMC+ approved this study (#143040). All participants gave informed consent to participate in the study.

#### Protocol amendments

Important protocol modifications, which may impact on the conduct of the study or may affect participant safety, including changes in study objectives, study design, study population, sample sizes, study procedures, or significant administrative aspects will require a formal amendment to protocol. Substantial amendments will be notified to the principal investigators and approved by the Medical Ethical Committee of the MUMC+ prior to implementation. Minor changes to the protocol that have no effect on the way the study is conducted will not be notified to the Medical Ethical Committee of the MUMC+, but will be recorded and filed by the investigators.

### Consent for publication

Not applicable.

### Availability of data

Not applicable.

### Availability of supporting data

Not applicable.

### SPIRIT Guidelines

This study protocol is based on the SPIRIT 2013 Statement [53]. A SPIRIT checklist is provided as an additional file.

## Appendix

**Table 3 Tab3:** Description of the ESM concepts, items and response choices in the daily, morning and evening questionnaire

Daily questionnaire		
Concept	Item	Rating scale
Positive affect	1. I feel cheerful	7-point scale (1 ‘not at all’ to 7 ‘very much’)
	2. I feel relaxed	7-point scale (1 ‘not at all’ to 7 ‘very much’)
	3. I feel enthusiastic	7-point scale (1 ‘not at all’ to 7 ‘very much’)
	4. I feel satisfied	7-point scale (1 ‘not at all’ to 7 ‘very much’)
Negative affect	5. I feel insecure	7-point scale (1 ‘not at all’ to 7 ‘very much’)
	6. I feel lonely	7-point scale (1 ‘not at all’ to 7 ‘very much’)
	7. I feel anxious	7-point scale (1 ‘not at all’ to 7 ‘very much’)
	8. I feel irritated	7-point scale (1 ‘not at all’ to 7 ‘very much’)
	9. I feel down	7-point scale (1 ‘not at all’ to 7 ‘very much’)
	10. I feel desperate	7-point scale (1 ‘not at all’ to 7 ‘very much’)
	11. I feel confident	7-point scale (1 ‘not at all’ to 7 ‘very much’)
	12. I feel tensed	-point scale (1 ‘not at all’ to 7 ‘very much’)
Self-esteem	13. I like myself	7-point scale (1 ‘not at all’ to 7 ‘very much’)
	14. I am ashamed of myself	7-point scale (1 ‘not at all’ to 7 ‘very much’)
	15. I doubt myself	7-point scale (1 ‘not at all’ to 7 ‘very much’)
	16. I am satisfied with myself	7-point scale (1 ‘not at all’ to 7 ‘very much’)
Physical well-being	17. I am tired	7-point scale (1 ‘not at all’ to 7 ‘very much’)
	18. I feel well	7-point scale (1 ‘not at all’ to 7 ‘very much’)
	19. I am in pain	7-point scale (1 ‘not at all’ to 7 ‘very much’)
	20. I have problems in walking	7-point scale (1 ‘not at all’ to 7 ‘very much’)
Activity	21. What am I doing? (just before the alert)	Doing nothing; resting; work; household; self care; caring for partner; active relaxation; passive relaxation; something else
	22. And also?	Doing nothing; resting; work; household; self care; caring for partner; active relaxation; passive relaxation; something else
	23. And…?	Doing nothing; resting; work; household; self care; caring for partner; active relaxation; passive relaxation; something else
	24. I like doing this	7-point scale (1 ‘not at all’ to 7 ‘very much’)
	25. I would rather be doing something else	7-point scale (1 ‘not at all’ to 7 ‘very much’)
	26. This is difficult for me	7-point scale (1 ‘not at all’ to 7 ‘very much’)
	27. I feel I am being active	7-point scale (1 ‘not at all’ to 7 ‘very much’)
	28. I can do this well	7-point scale (1 ‘not at all’ to 7 ‘very much’)
	29. I am doing this activity together with my partner	Yes; no
Location	30. Where am I?	At home; at family’s/friend’s place; at work; health care setting; public place; transport; somewhere else
Social company	31. Who am I with?	Partner; family; friends; colleagues; health care professional; acquaintances; strangers/others; nobody
	32. With whom else?	Partner; family; friends; colleagues; health care professional; acquaintances; strangers/others; nobody
	33. And…?	Partner; family; friends; colleagues; health care professional; acquaintances; strangers/others; nobody
	*Branching questions in case of being in company:*	
	34. I would prefer to be alone	7-point scale (1 ‘not at all’ to 7 ‘very much’)
	35. I think my company is pleasant	7-point scale (1 ‘not at all’ to 7 ‘very much’)
	36. I feel at ease in this company	7-point scale (1 ‘not at all’ to 7 ‘very much’)
	*Branching questions in case of being alone:*	
	34. I would prefer to be in company of others	7-point scale (1 ‘not at all’ to 7 ‘very much’)
	35. I enjoy being alone	7-point scale (1 ‘not at all’ to 7 ‘very much’)
	36. I feel at ease being alone	7-point scale (1 ‘not at all’ to 7 ‘very much’)
Events	37. Since the last alert the most important thing that happened is…	(take an event in mind before you continue)
	38. How pleasant was this event?	bipolar scale (−3 ‘very unpleasant’ to +3 ‘very pleasant’)
	39. I had this situation under control	7-point scale (1 ‘not at all’ to 7 ‘very much’)
	40. Was this situation unexpected?	7-point scale (1 ‘not at all’ to 7 ‘very much’)
	41. The event was important to me	bipolar scale (−3 ‘very unimportant’ to +3 ‘very important’)
	42. With whom was I?	Partner; nobody; someone else
General	43. This alert disturbed me	7-point scale (1 ‘not at all’ to 7 ‘very much’)
Morning questionnaire		
	1. I slept well	7-point scale (1 ‘not at all’ to 7 ‘very much’)
	2. How long did it take before I fell asleep	0–5 min; 5–15 min; 30–45 min; 45–60 min; 1-2 h; 2 4 h; >4 h
	3. How often did I wake up last night	1 time; 2 times; 3 times; 4 times; 5 times; more than 5 times
	4. My partner disturbed my sleep	7-point scale (1 ‘not at all’ to 7 ‘very much’)
	5. I feel rested	7-point scale (1 ‘not at all’ to 7 ‘very much’)
	6. I feel apprehensive about today	7-point scale (1 ‘not at all’ to 7 ‘very much’)
Evening questionnaire		
	1. This was an ordinary day	7-point scale (1 ‘not at all’ to 7 ‘very much’)
	2. If I had not had the device, I would have done different things today	7-point scale (1 ‘not at all’ to 7 ‘very much’)
	3. I generally felt well today	7-point scale (1 ‘not at all’ to 7 ‘very much’)
	4. I generally felt tired today	7-point scale (1 ‘not at all’ to 7 ‘very much’)
	5. I generally felt tensed today	7-point scale (1 ‘not at all’ to 7 ‘very much’)
	6. I generally worried a lot today	7-point scale (1 ‘not at all’ to 7 ‘very much’)
	7. I generally felt able to manage today	7-point scale (1 ‘not at all’ to 7 ‘very much’)
	8. My health state was good today	Visual Analogue Scale (0 ‘worst imaginable health’ to 100 ‘best imaginable health’)
	9. How many hours did you spend on caring for your partner today (incl. supervision)	0 h; 1 h; 2 h; 3 h; 4 h; 5 h; >5 h
	10. Today I felt strained in the interactions with my partner	7-point scale (1 ‘not at all’ to 7 ‘very much’)
	11. Today I felt stressed due to my care responsibilities	7-point scale (1 ‘not at all’ to 7 ‘very much’)
	12. Today I felt that the situation with my partner did not allow me as much privacy as I would have liked	7-point scale (1 ‘not at all’ to 7 ‘very much’)
	13. Today I had enough time for myself	7-point scale (1 ‘not at all’ to 7 ‘very much’)
	14. Today I was in need of support	7-point scale (1 ‘not at all’ to 7 ‘very much’)
	15. Today I received enough support	7-point scale (1 ‘not at all’ to 7 ‘very much’)
	*Today, to what extent did your partner suffer from:*	
	16. Being sad or depressed	7-point scale (1 ‘not at all’ to 7 ‘very much’)
	17. Being anxious our nervous	7-point scale (1 ‘not at all’ to 7 ‘very much’)
	18. Acting impulsively or embarrassing	7-point scale (1 ‘not at all’ to 7 ‘very much’)
	19. A loss of interest in activities/other people	7-point scale (1 ‘not at all’ to 7 ‘very much’)
	20. Being irritated or impatient	7-point scale (1 ‘not at all’ to 7 ‘very much’)
	21. Being too cheerful for no reason	7-point scale (1 ‘not at all’ to 7 ‘very much’)
	22. Being restless	7-point scale (1 ‘not at all’ to 7 ‘very much’)
	23. Agitation/aggression	7-point scale (1 ‘not at all’ to 7 ‘very much’)
	24. Beliefs that you know are not true	7-point scale (1 ‘not at all’ to 7 ‘very much’)
	25. Seeing false visions or hearing false voices	7-point scale (1 ‘not at all’ to 7 ‘very much’)

